## Abstract

**Background:**

About 30% of cancer survivors suffer from chemotherapy-induced peripheral neuropathy (CIPN) ≥6 months after completion of chemotherapy. This condition, for which treatment options are scarce, comes with limitations in daily life functioning and decreased quality of life. The current study examines the effectiveness of an online self-help intervention based on Acceptance and Commitment Therapy (ACT) in comparison to a waiting list condition (WLC) to deal with CIPN. In addition, it examines which factors moderate effects and to what extent the effects differ between guided and unguided ACT intervention.

**Methods:**

A two-parallel, non-blinded randomized controlled trial (RCT) will be carried out. Adult cancer survivors who experience painful CIPN for at least 3 months and completed chemotherapy at least 6 months ago will be recruited (*n*=146). In the intervention condition, participants will follow an 8-week self-management course containing 6 modules regarding psychoeducation and ACT processes, including therapeutic email guidance. By means of text and experiential exercises, supplemented with illustrations, metaphors, and audio files, people will learn to carry out value-oriented activities in their daily life with pain. Participants will learn new ways of coping with pain, including reducing pain avoidance and increasing pain acceptance. Participants in the WLC will be invited to follow the intervention without therapeutic guidance 5 months after start. Pain interference is the primary outcome, while psychological distress, quality of life, CIPN symptom severity, pain intensity, psychological flexibility, mindfulness skills, values-based living, and pain catastrophizing will serve as secondary outcomes. All outcome measures will be evaluated at inclusion and baseline, early-intervention, mid-intervention, post-treatment, and 3- and 6-month post-treatment. Qualitative interviews will be conducted post-treatment regarding experiences, usage, usability, content fit, and satisfaction with the intervention.

**Discussion:**

This study will provide valuable information on the effectiveness of an online self-help intervention based on ACT versus WLC for chronic painful CIPN patients.

**Trial registration:**

ClinicalTrials.gov NCT05371158. Registered on May 12, 2022.

Protocol version: version 1, 24-05-2022

**Supplementary Information:**

The online version contains supplementary material available at 10.1186/s13063-022-06592-3.

## Background

The number of cancer survivors continues to grow [1–5] as the population ages, early detection through screening rises, and cancer survival rates improve [6]. Many of these survivors face long-term side effects of cancer and its treatment, whereby their quality of life (QoL) is strongly affected [1, 7]. Chemotherapy can cause multiple disabling long-term side effects like chemotherapy-induced peripheral neuropathy (CIPN) [8]. CIPN can occur due to the use of certain chemotherapeutic agents, such as taxanes, platinum compounds, and vinca alkaloids [9]. CIPN presents itself with symptoms such as tingling, numbness, cramps, and aching or burning pain in the hands and feet, which can also spread to arms and legs [10–12]. Up to 80% of cancer survivors suffers from CIPN 1 month after chemotherapy, which stabilizes to around 30% at 6 months or longer after chemotherapy [7, 8, 13–16]. This prevalence differs between cancer types (range 10–60%). As the application of chemotherapy in cancer treatment is rising, CIPN is likely to become one of the most common long-term side effects for cancer survivors [17]. CIPN is a very limiting condition, as a systematic review has shown that CIPN negatively influences QoL in adult cancer survivors [7]. Patients can experience impaired QoL due to CIPN up to 11 years after chemotherapy, caused by the decreased performance of regular activities, depressive symptoms, and poor sleep quality [18–21]. In addition, it has been shown that specifically *painful* CIPN is associated with lower QoL compared to non-painful CIPN [22].

In order to improve the patients’ QoL, cognitive behavioral therapies (CBT), like third-generation CBTs as Acceptance & Commitment Therapy (ACT), are increasingly used in global cancer care [23, 24]. ACT helps patients to shift focus towards engaging in personally valuable activities by increasing pain acceptance [25] and has been shown to be effective for other types of chronic pain [26]. Although the effectiveness of online ACT interventions has not yet been investigated for chronic painful CIPN patients, a previous study found that treatment with online CBT positively affected pain intensity in this patient group, creating positive expectations for treatment with online ACT as well [27]. Traditional *face-to-face* psychological therapies have some drawbacks, such as high costs, not being accessible or hardly available, having to travel to the therapist, negative stigma, and high psychological burden [27, 28]. Due to developments in the field of eHealth, these obstacles can be mitigated [27–29]. That is, with the use of online self-management interventions, patients are able to receive psychological therapy whenever and wherever they would like to, without having to travel to a therapist [27, 28]. Online self-management interventions offer the additional benefit of augmented protection of patients’ anonymity and privacy [29].

Even though online interventions are relatively new, several such interventions have demonstrable effectivity in improving QoL in cancer patients and survivors [28, 30–32]. A randomized controlled trial (RCT) has shown that the use of an online CBT intervention significantly improved CIPN pain intensity and may be effective [27]. Furthermore, research has shown that online interventions based on ACT are capable of improving pain intensity, pain interference, pain catastrophizing, disability, depression, anxiety, psychological inflexibility, and QoL in chronic pain patients with a variety of pain diagnoses (e.g., fibromyalgia, rheumatoid arthritis, and back complaints) [33, 34]. These findings suggest that an online self-help intervention based on ACT might be effective for adult cancer survivors with chronic painful CIPN as well. However, effects may differ between patients, since previous research has shown factors such as pain intensity, depressive and anxiety symptoms, and emotional well-being to predict the effectiveness of online ACT for chronic pain [35], and the extent to which patients benefit from the online intervention may hence vary. Furthermore, there may also be differences in the effectiveness with different types of the online intervention, namely with or without guidance. Earlier research has shown that guidance, including feedback, explanations, motivations and reminders, improves treatment effects compared to unguided interventions [36, 37]. The primary aim of this study researching the online intervention named ‘Embrace Pain’ is to reduce pain interference in cancer survivors with chronic painful CIPN. To study this, three objectives have been formulated:*Objective 1:* To examine the effectiveness of an online self-help intervention based on ACT for reducing pain interference in cancer survivors with chronic painful CIPN in a randomized controlled trial (RCT) and compare this to a waiting list condition (WLC).*Objective 2:* To examine which baseline demographic, clinical, and psychosocial factors may moderate the effectiveness of an online self-help intervention based on ACT.*Objective 3:* To examine the extent to which effects differ between guided and unguided versions of the online self-help intervention based on ACT.

## Methods

### Study design

An RCT will be carried out with two parallel, non-blinded groups. Participants will be involved in the study for a duration of 8 months from the first to the last measurement. Outcome measures will be collected at baseline (T0), early-intervention (T1; 3 weeks after baseline), mid-intervention (T2; 6 weeks after baseline), directly at the end of intervention (T3; 2 months after baseline), and through two follow-up measurements (T4; 3 months after the intervention, T5; 6 months after intervention). A flowchart of the study is shown in Fig. 1.

**Fig. 1 Fig1:**
[figure not shown]
Flowchart

### Study population

Inclusion criteria consist of (a) age of 18 years or older and (b) identified by a clinician or self as having painful sensations (i.e., aching, burning, “pins-and-needles”, shock-like, painful tingling, numbness, cramps) bilaterally in the feet/legs and/or hands/arms for at least 3 months. Furthermore, (c) a score of 3 or higher on an 11-point pain intensity scale (Numeric Rating Scale), (d) the pain was not present prior to receiving chemotherapy, (e) chemotherapy ended at least 6 months ago, and (f) a score of 1 or higher on EORTC QLQ–CIPN20. Exclusion criteria are (a) enrollment in psychological treatment related to cancer, pain, or psychological disorders upon entry; (b) new chemotherapy scheduled during study participation; (c) no access to the Internet/no email address; (d) not enough time to follow the intervention (2 h per week); and (e) according to patient’s own perception no problems with the Dutch language.

### Recruitment

Patients will be recruited through a flyer with a QR code and a link to a website. These flyers will be distributed in various ways (in the Netherlands): online media (e.g., Kanker.nl, Facebook groups for neuropathy, patient associations), hospital waiting rooms (e.g., oncology departments, AYA centers, pain clinics), and through other healthcare providers (e.g., oncological foot care providers). Interested patients can visit the recruitment website where they can read more information and sign up if interested.

When a patient is interested in participation, the patient will receive an information letter and an informed consent form by mail, sent by a research assistant. The informed consent also includes information regarding the collection and use of participant data in follow-up studies. Afterwards, the participant will receive a questionnaire (T0a) regarding inclusion criteria, to examine whether the participant is eligible to participate. Additionally, patients must achieve certain scores on several questionnaires, namely Numeric Rating Scale ≥2 and EORTC QLQ–CIPN20 ≥1. If the questionnaire from T0a shows that respondents are not suitable for participation, they will be notified with a rejection and along with it the reason for rejection based on the relevant inclusion or exclusion criterion.

### Randomization

When the patient is admitted to the study, the patient will receive confirmation of participation, the result of randomization, and the baseline questionnaire (T0b). Patients will be randomized to receive either ACT or WLC. The study will stratify by age and sex by means of block-wise randomization. An online generator will be used for this. Randomization will be performed by a research associate.

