### Waiting list condition

The control condition includes a WLC. At 5 months after start (i.e., T4) participants in the WLC receive the opportunity to follow the intervention without email guidance by a therapist. They neither receive a welcome letter at the start, which means that they only read the introduction about the training before starting.

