### Outcomes

Questionnaires will be completed online via the PROFILES Registry [38]. Patients will receive reminders via email to promote participant retention and complete follow-up. A complete overview of enrolment, interventions, and outcome measurements is shown in Table 2.

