### Statistical analysis

#### Primary analyses

Significant differences at baseline between the conditions will be checked by performing one-way ANOVA’s and chi-square tests.

Effects of the intervention on all outcomes will be assessed by performing intention-to-treat analyses using general linear mixed models. Baseline to post-intervention and 3- and 6-month follow-up differences will be used as repeated measures, with treatment (2 levels), time (3 levels) and their first-order interactions as fixed factors. Confidence intervals of 95% will be calculated for all outcomes. Drop-out and non-adherence are relatively common in online interventions [56]. Therefore, secondary analyses will be performed to examine effects on outcome variables for participants who adhered to the intervention (i.e., all session completed and self-reported minimum of 2 h per week spent on intervention). At post-intervention and follow-up, effect sizes (Cohen’s *d*) will be calculated using means and standard deviations. Effect sizes of 0.80 are considered large, effect sizes of 0.50 are evaluated as moderate, and effect sizes of 0.20 are considered small [57].

Initiative on Methods, Measurement, and Pain Assessment in Clinical Trials (IMMPACT) recommendations will be followed to evaluate the proportion of participants showing clinically significant change [58]. Clinical improvement will be assessed with missing values imputed by the Expectation Maximization-algorithm. Proportions of clinically improved participants and Chi-square tests will assess statistically significant differences in the proportions for the two conditions. It will be calculated for (a) pain interference (MPI – Interference), (b) pain intensity (NRS), and (c) CIPN symptom severity (EORTC QLQ – CIPN 20). A decrease of at least 0.6 standard deviation will be assessed as evidence of clinically significant change for the MPI – Interference scale, based on the IMMPACT guidelines [58]. Decreases of 20% or higher in pain intensity (NRS) will be assessed as minimum and moderate changes. No specific IMMPACT guidelines exist for the HADS. Therefore, a distribution-based decrease of at least 1 standard error of the mean is recommended [58].

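### Allocation is disclosed together with the T0b baseline questionnaire, so the baseline for the primary outcome is answered with knowledge of the assigned arm

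*Protocol article*

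**What the plan says.** **Order of events.** Under Recruitment, after consent, "the participant will receive a questionnaire (T0a) regarding inclusion criteria, to examine whether the participant is eligible to participate". The scales named at that step are two: "patients must achieve certain scores on several questionnaires, namely Numeric Rating Scale ≥2 and EORTC QLQ–CIPN20 ≥1". Under Randomization, once admitted, "the patient will receive confirmation of participation, the result of randomization, and the baseline questionnaire (T0b". Nothing in the article makes the return of T0b a condition for randomising or for releasing the allocation.

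**Setting.** Study design: "An RCT will be carried out with two parallel, non-blinded groups". Outcomes: "Questionnaires will be completed online via the PROFILES Registry". The Waiting list condition section shows how different the two messages are. One arm starts guided treatment now; for the other, "At 5 months after start (i.e., T4) participants in the WLC receive the opportunity to follow the intervention without email guidance".

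**Use of baseline.** Primary analyses: "Baseline to post-intervention and 3- and 6-month follow-up differences will be used as repeated measures", with treatment at two levels and time at three. The same section defines clinical improvement on MPI Interference as a fall of at least 0.6 SD. Secondary analyses compare the guided and unguided versions on change from baseline to the 3-month follow-up, with the baseline score as control variable. Objective 2 in the Background is "To examine which baseline demographic, clinical, and psychosocial factors may moderate the effectiveness".

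**The concern.** Awareness of allocation after randomisation cannot be avoided with a waiting list. Awareness before the baseline measurement can. A baseline taken before disclosure can differ between arms only by chance. A baseline taken after it may also contain a reaction to the news, such as disappointment at waiting or optimism about starting.

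Four things are at stake:
- **Primary estimate:** T0b is subtracted from each follow-up value, so a reaction at T0b enters the treatment contrast.
- **Baseline comparisons:** the planned tests between conditions could not tell chance imbalance from a reaction to allocation.
- **Moderators:** psychosocial scores used for Objective 2 may already depend on the arm.
- **Retention:** return of T0b may differ by arm after randomisation, since the news is less welcome in one arm.

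**Working it through.** **1. Is MPI Interference measured before disclosure anywhere?** T0a is described as an eligibility check, and only NRS and CIPN20 are named as scored there. The article itself calls T0b the baseline questionnaire. Nothing shown places MPI Interference before disclosure.

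**2. Is baseline really subtracted?** Post-intervention, 3-month and 6-month follow-up give three differences from baseline, which matches time at three levels. Had baseline been a time point in the model, there would be four. With baseline as a fourth time level and arm means left free there, the treatment-by-time interaction would subtract it again.

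**3. Bias formulas.** Let knowledge of allocation shift mean T0b between arms by b SD, with no effect at follow-up (a transient shift). Let r be the correlation between baseline and follow-up, with equal SDs.
- Change-score contrast: bias = b in size.
- Baseline-adjusted contrast: bias ≈ r × b in size.
- If a fraction p of the shift persists to follow-up, the change-score bias falls to (1 − p) × b.

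**4. Size against the design effect.** The Sample size calculation gives d = 0.50 and 51 per group at follow-up. The documents give neither b nor r, so the values here are assumptions.
- b = 0.1: 0.1/0.5 = 20% of the target effect.
- b = 0.2: 0.2/0.5 = 40% of the target effect.
- With adjustment at r = 0.5: 0.5 × 0.1 = 0.05 SD and 0.5 × 0.2 = 0.10 SD, or 10% and 20% of the target.
- Against the 0.6 SD responder threshold, 0.2/0.6 is one third.

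**5. Effect on the test if ACT has no true effect.** The chance of rejection is P(|Z| > 1.96), with Z centred at bias/SE. With n = 51 per arm, √(2/51) = 0.198. For change scores SE = √(2(1 − r)) × 0.198; for the adjusted contrast SE = √(1 − r²) × 0.198. At r = 0.5 and b = 0.2, the change-score SE is 0.198 and bias/SE = 1.01, which gives 17.3%.

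| Assumed r | Assumed b (SD) | Change score | Baseline-adjusted |
|---|---|---|---|
| 0.5 | 0.1 | 8.0% | 6.0% |
| 0.5 | 0.2 | 17.3% | 9.0% |
| 0.7 | 0.1 | 10.0% | 7.9% |
| 0.7 | 0.2 | 25.6% | 16.8% |

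The nominal rate is 5%. The excess rejections fall mainly on the side to which the bias points. The 51 per group is taken as stated: it matches a one-sided t-test, while a two-sided one needs 64. That is a separate matter and does not change the bias in step 3.

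**6. Direction.** Lower interference is better. If disappointment raises T0b on the waiting list, that arm later shows a larger fall. If optimism lowers T0b in the ACT arm, that arm shows a smaller fall. Both understate the ACT effect. Higher reporting at T0b in the ACT arm, or lower reporting on the waiting list, would overstate it.

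**7. Which moderators are exposed?** Sex, age, education, number of comorbidities and time since CIPN onset should hardly respond to learning the allocation. NRS and CIPN20 have screening scores. That leaves distress, psychological inflexibility, mindfulness, values-based living, catastrophizing and quality of life.

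**The case against.** The strongest reply is that the size of the harm is unproven and parts of it may not arise.

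- **Not all baselines are affected.** A reader might infer that every change score rests on a post-disclosure baseline. The documents do not support that: NRS and CIPN20 are scored at T0a, and the Abstract lists inclusion and baseline together as an assessment time. Table 2, which would show the content of T0a and T0b, is not available here. This stands and limits the point to MPI Interference and the other scales not shown at T0a.
- **Analysis can help.** A reader might infer that the bias cannot be removed at analysis. That is too strong. A randomised comparison of follow-up scores does not depend on T0b, and baseline adjustment shrinks the bias to about r × b. What remains true is that an analysis using T0b as baseline is exposed.
- **Direction.** A reader might infer a spurious benefit of ACT. The most obvious reactions point the other way, towards understatement, and a shift that persists to follow-up cancels in part or in full.
- **Missing T0b.** A reader might infer that people who do not return T0b are dropped from the intention-to-treat analysis. A person without T0b has no difference score, but a condensed article need not describe how a missing baseline is handled. Arm-dependent non-return is a risk, not a documented result.
- **An unstated safeguard.** The full protocol may hold the allocation until T0b is in. The article's wording points the other way, and one sentence would settle it.

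None of this changes the stated order for the primary outcome.

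**Conclusion.** The point holds in a limited form. As written, participants learn their arm no later than they receive T0b, and nothing shown places the primary outcome's baseline before that. The sequence follows directly from the text; its impact is uncertain. With an assumed transient shift of 0.1 to 0.2 SD, the change-score contrast is biased by 20% to 40% of d = 0.50, and the adjusted contrast at an assumed r = 0.5 by half of that. These figures illustrate sensitivity and are not evidence that such a shift occurs. The direction is unknown. Psychosocial moderators and the completeness of T0b are exposed as well. The problem is avoidable and cheap to prevent, which is the reason to act although its size cannot be established.

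**What to change.** **Further enrolments.** Send T0b after T0a eligibility is confirmed, randomise only once T0b has been received, then disclose allocation. State this order in the protocol. If it is already the practice, one clarifying sentence is enough.

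**Participants enrolled under the current order** (recruitment began in December 2021). Prespecify a sensitivity analysis of follow-up scores that does not use T0b, adjusted for age, sex and the T0a NRS and CIPN20 scores, and report whether the main result depends on T0b. It needs no new data. It cannot recover people lost to all follow-up, and it remains open to the ordinary reporting bias of a non-blinded trial.

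**Reporting.** Give the number not returning T0b by arm for those randomised before the change, and describe both baseline procedures.

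**Cost.** A short amendment, a reordered mailing and a short delay to allocation. People who do not return T0b are lost before randomisation, so somewhat more may need screening to reach 146, but the randomised comparison stays intact. A change during recruitment leaves two baseline procedures within one trial.

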### Intervention

The experimental condition includes an online psychological intervention with therapist email guidance based on ACT. The intervention can be worked through by the patient from home or at another location of choice, in a webpage or app by logging in with an email and self-created password. Participants receive a welcome letter from the supervisor. It consists of 6 modules which can be worked through in 8 weeks. The intervention primarily consists of text and experiential exercises, complemented with illustrations, metaphors, and audio (mp3) files. Before starting the module, participants read an introduction about the training. The first module includes psychoeducation on neuropathic pain and CIPN (Table 1). Participants will be provided with information to familiarize themselves with intervention goals and mindfulness exercises central to ACT. In subsequent modules, participants will learn about the aversive effects of pain avoidance, gain insight into their personal values, and work on pain acceptance. Throughout the intervention, participants will exercise to recognize unhelpful thoughts about their pain and learn the difference between the subjective (judging) and objective self, create activities that align with values, and think about concrete actions to prevent relapse. When access to the online environment is terminated, participants can no longer view the online environment or communicate with the supervisor. However, participants can always continue to view the session they submitted.

**Table 1 Tab1:** Schematic overview of modules of the ACT intervention

Module	Therapeutic processes	Information	Assignments	Audio files (mindfulness)
Welcome		Online environment, contact, additional help, other long-term consequences, and tips.		
1: Chronic neuropathic pain	Psychoeducation	CIPN and chronic pain		A: Concentration on breathing
2: On the way to values	Values	Values and valued-based activities	I: Explore your values II: My values III (optional): My values in pictures	A: Body exploration
3: Away from my values	Pain avoidance	Avoidance and managing pain	I: My ways of avoiding II: Moment when I am in pain	A: Concentration on breathing B: Body exploration C: Three-minute breathing space
4: On the road with skills	Commitment and Defusion	Learning how to deal with pain differently	I: Acceptance in action II: Your recurring thoughts of pain III: Is the thought useful? IX (optional): Struggle or open up	A: Allowing what is
5: Taking a new road	Committed action	Converting values to behaviors in different life areas and devising valued-based activities	I: My ACT matrix	A: Concentration on breathing B: Body exploration C: Three-minute breathing space D: Allowing what is
6: On the road to values: from day to day	Social context	Perform actions in daily life and long-term changes	I: Your communication about pain II: Self-care	A: Three-minute breathing space B: Notice five things C: Brushing your teeth with attention

Participants in the experimental condition will receive guidance from Psychology master’s students from Tilburg University, who will be first trained and then supervised by a licensed healthcare psychologist. In addition, they receive supervision in the first weeks of providing guidance. Also, they will always have the possibility to ask for advice from a licensed clinical psychologist during the intervention. There will also be a backup in case of possible psychological problems that require more help. In that case, the licensed clinical psychologist will be informed and asked for advice. Guidance of participants will occur via email. Contact will be without obligation. It is possible to send an email every week in the protected environment of the online intervention, which complies with all privacy conditions as stated by the GDPR. Guidance is mainly intended for feedback related to the exercises made, answering questions about the content, and maintaining motivation to continue with the intervention. Here the choice lies with the participant, but facilitators will continue to encourage questions throughout the training.

